**Methods:**

CHIME is an observational cohort study where participants attend 2 visits prior to initiating the HC method of their choice, and then attend 6 visits over 12 months with biological sampling (vaginal swabs, cervicovaginal lavage, cytobrush and blood) for immunological, bacteriological, and virological analyses at each visit. Immune profiling will be evaluated by multi-color flow cytometry to determine how different T-cell subsets, in particular the CD4 T-cell subsets, change during the course of contraceptive use and whether they have different profiles in the FGT compared to the systemic compartment. The study aims are (1) to characterize the alterations in FGT and systemic immune profiles associated with three long-acting progestin-only HC and (2) to evaluate the vaginal microenvironment, determined by 16 s rRNA sequencing, as an individual-level risk factor and moderator of genital and systemic immune profile changes following exposure to three commonly used HC. Data collection started in March 2019 and is scheduled to be completed in October 2024.

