A diagnosis of BV often indicates an abundance of diverse microbial species and communities rather than a single species in the FGT. Historically, BV was diagnosed using clinical criteria (Amsel’s criteria) or gram stain to identify altered microbiota. Genetic sequencing technology, including 16 s rRNA sequencing, provides granular detail on genus and species alterations that previously were unavailable and may be more informative. These more sensitive microbiome techniques offer an opportunity to improve understanding of the microenvironment at the species level.

Supra-physiologic levels of exogenous sex steroids are capable of modulating FGT mucosal immunity [51–54]; however, these effects are not consistently observed across all studies [55]. Inconsistencies may be attributable to the influence of additional modifying factors, especially the vaginal microenvironment [56]. This study will test the hypothesis that the vaginal microenvironment has an important modifying role in the relationship between HC and HIV risk. Further, we seek to characterize the vaginal microenvironment using gram stain criteria and, additionally, using the more sensitive 16 s rRNA techniques to identify specific bacterial species or community state types capable of modifying HIV risk. Understanding this interplay may provide opportunities for targeted interventions to alter the composition of the vaginal environment and potentially modify the STI/HIV acquisition risk with HC.

The study tests the overarching hypothesis that hormonal contraceptives induce systemic and mucosal immune changes capable of altering susceptibility or response to diseases, including HIV infection, and that these effects vary in nature and magnitude by contraceptive type and will be modified by the vaginal microenvironment. Our study objectives are [1] to characterize the alterations in female genital and systemic immune profiles associated with three long-acting progestin-only HC methods: DMPA, ENG-implant, and LNG-IUD; and [2] to evaluate the vaginal microenvironment as a moderator of genital and systemic immune profile changes following exposure to these three commonly-used hormonal contraceptives.

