### Data analysis

Univariate analyses will evaluate for differences in pre-contraception participant characteristics by HC method (DMPA, ENG-implant, LNG-IUD). If meaningful differences are observed, inverse propensity score weighting will be used to weight participants so that the study arms are more similar on pre-contraceptive participant characteristics. To account for repeated measures with a participant, all analyses will use mixed models with an appropriate distribution (normal, beta) and link function (identity, log), use an unstructured covariance matrix, and include a random effect for participant. For Aim 1, the primary outcome of interest is proportion of CCR5 expressing CD4^+^ T cells, while secondary outcomes are other immunologic outcomes from the flow cytometry and immune-related protein assays characteristics that may provide deeper insight into immune regulation in the FGT. Separate models for each outcome will contain time (categorical: visit 1, 2, 3, 4, 5, 6, 7, 8), contraceptive method (DMPA, ENG-implant, LNG-IUD), and a method by time interaction term. Models will additionally include important covariates such as age, race, STI presence, menstrual cycle characteristics and, if needed, incorporate propensity score weights. Model-based estimates of the change in mean outcome level within a contraceptive method over time (visit 1 and 2 versus each of 3, 6, and 12 months after contraceptive administration) will be computed. If the interaction term of method by time is significant, model-based comparisons of the means by contraceptive method and time (visit 1 and 2 versus each of: 3, 6, and 12 months after contraceptive administration) will also be computed pairwise for all possible combinations. Statistical significance will be set at α = 0.05 for the primary outcome of CCR5 and the main effects (contraceptive method, time) and the interaction term (method by time). Secondary outcomes will be evaluated for direction and magnitude of the associations. Models will be stratified by each specimen type (blood, CVL, cytobrush, biopsy).

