For Aim 2, we will evaluate alpha diversity at each time point, using the Shannon diversity index and Chao1 measures. We will also investigate microbiome CST over time. We will use additional statistical tools, such as a Principal Component Analysis to visualize clustering of the data based on distance metrics (weighted Unifrac, Bray–Curtis) [75] and advanced tools such as scree plots to identify the specific taxa that account for group differences. We will evaluate for effect modification on the microbial outcomes, such as BV status (BV presence or absence based on Nugent Score), species diversity, CST, and specific bacterial species by including interaction terms, separately and stratified by contraceptive method. An indicator for each outcome and an outcome by time interaction term will be added to the contraceptive method stratified mixed models. If the outcome by time interaction term is significant, model-based comparisons of the means by outcome and time (visit 1 and 2 versus each of: 3, 6, and 12 months after contraceptive administration) will also be computed pairwise for all possible combinations. As the primary independent variable of interest is BV, statistical significance will be set at α = 0.05 for the main effects (BV, time) and interaction term (BV by time) from the repeated measures analysis for CCR5 expression.

Analyses will be conducted using SAS software (SAS Institute, Cary, NC) and R (R Core Team).

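### The abstract asks whether genital and systemic T-cell profiles differ, but models are fitted separately by specimen type, so the plan yields no interval or test for that difference

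*Protocol article*

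**What the plan says.** The question is stated in the Methods part of the abstract. Flow cytometry is to show how T-cell subsets change during contraceptive use and "whether they have different profiles in the FGT compared to the systemic compartment".

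The numbered aim in the same paragraph is softer: "to characterize the alterations in FGT and systemic immune profiles associated with three long-acting progestin-only HC". The objective at the end of the Background matches it: "to characterize the alterations in female genital and systemic immune profiles associated with three long-acting progestin-only HC methods". Neither sets one compartment against the other.

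The Data analysis section fixes the analysis:

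- Model class: "all analyses will use mixed models with an appropriate distribution (normal, beta) and link function (identity, log"), with a random effect for participant.
- Aim 1 fixed effects: time, "contraceptive method (DMPA, ENG-implant, LNG-IUD), and a method by time interaction term", plus covariates.
- Tests given α = 0.05 for CCR5: "the main effects (contraceptive method, time) and the interaction term (method by time").
- Specimens: "Models will be stratified by each specimen type (blood, CVL, cytobrush, biopsy").
- Aim 2: "An indicator for each outcome and an outcome by time interaction term will be added to the contraceptive method stratified mixed models".

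The section also plans model-based estimates of change within each method, from visits 1 and 2 to 3, 6 and 12 months. Under the stratification, these are produced once per specimen type.

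**The concern.** A comparison of compartments needs a quantity that crosses specimens: the change in an FGT specimen against the change in blood, in the same women. The stated models contain no specimen term, so this quantity never appears with a standard error.

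The design invites such a claim. The Background notes that systemic levonorgestrel is low with the LNG-IUD and that the effect of higher local concentrations is unknown. A finding that CCR5 rose in CVL but not in blood would be read as a local effect. If it rests on one significant and one non-significant result from separate models, the two changes may not differ at all.

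**Working it through.** **Step 1: is there a cross-specimen analysis anywhere in the article?**

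| Place | What is planned | Specimen term or contrast |
|---|---|---|
| Data analysis, Aim 1 | time, method, method by time, covariates | none; one model per specimen |
| Data analysis, 75-woman subset | extra markers on cytobrush and blood; exploratory principal components, gating, viSNE, SPADE | none |
| Data analysis, Aim 2 | microbial indicator and its interaction with time, within method | none |
| Power/sample size, Aim 1 | method by time, from CVL pilot data | none |
| Power/sample size, Aim 2 | BV interaction | none |

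**Step 2: would the data support one?** Table 2 schedules blood sampling, genital sampling and flow cytometry at each of visits 1 to 8, so blood is paired by design with CVL and cytobrush. Biopsy is optional and taken only at visits 2, 4, 6 and 8. Immune cell characterization reports markers as a percentage of CD4+ cells, a scale common to all specimens.

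**Step 3: can the separate outputs stand in for the contrast?** The article states no figure for this comparison, so there is none to reproduce. What follows is an illustration on assumed inputs.

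Let each compartment's test have power p, with the same true effect, two-sided α = 0.05 and correlation r between the two estimates. For independent tests, the chance that exactly one is significant is 2p(1 − p):

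- p = 0.80: 2 × 0.80 × 0.20 = 0.32
- p = 0.92: 2 × 0.92 × 0.08 = 0.147

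For correlated tests, 400,000 pairs of bivariate normal statistics were drawn, each with mean z(0.975) + z(p) and unit variance. The direct contrast was (Z1 − Z2)/√(2 − 2r).

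| Power per compartment | r = 0 | r = 0.3 | r = 0.6 | Direct contrast, false positives |
|---|---|---|---|---|
| 80% | 32% | 27% | 20% | about 5% |
| 92% | 15% | 13% | 10% | about 5% |

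**Step 4: can a reader build the interval from the separate models?** Only the point estimate. With equal standard errors of 1, the difference has standard error √(2 − 2r), and separate models do not report r. Taking r = 0 gives √2. The resulting interval is too wide by √2/√1.4 = 1.20 if r = 0.3, and by √2/√0.8 = 1.58 if r = 0.6.

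**Step 5: does the scale matter?** Yes. Power/sample size defines a meaningful change relatively, as 50%. From the CVL pre-contraceptive mean of 23.0%, that is 0.5 × 23.0 = 11.5 points. From a blood baseline B, which the article does not give, it is 0.5 × B points. Equal relative changes are equal in points only if B = 23.0. Data analysis allows identity or log links, so the contrast must name its scale.

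**The case against.** The strongest reply is that the comparison is one clause in an abstract. The numbered aim and objective ask only for a characterization of both compartments. The overarching hypothesis has effects vary by contraceptive type and be modified by the vaginal microenvironment; it does not mention compartment. Stratified models deliver that aim. They are also a reasonable choice for specimens that may differ in level and variance, and a fuller plan that is not shown could hold a further contrast. This stands as a limit on weight: the question is secondary. It does not remove the mismatch, because the article itself states both the question and the handling of specimen type.

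Several stronger readings are not supported:

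- A reader might infer that the plan gives no estimate at all. It gives specimen-specific changes, and their difference can be had by subtraction. What is missing is the interval and test.
- A reader might infer that all four specimens are paired at every visit. Biopsy is not, and the Discussion reports missed visits and early terminations, so even the blood and CVL pairing is as scheduled rather than as achieved.
- A reader might attach the stated 92% power to a CVL-versus-blood comparison. That figure is for the three-method by pre/post interaction, from CVL pilot data. The article gives no power for blood or for within-method change.
- A reader might infer that the authors intend to compare p-values across specimens. Nothing says so. Alpha is confined to CCR5, and secondary outcomes are to be judged on the sign and size of associations.

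**Conclusion.** The point holds as a mismatch of modest weight between a stated question and a stated analysis. The plan produces specimen-specific changes but no interval or test for FGT versus blood, and it leaves the within-woman pairing of blood with CVL and cytobrush unused. It would be wrong to conclude that the primary CCR5 method-by-time analysis or the numbered aim is undermined; neither depends on a cross-specimen contrast.

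The possible error is a false claim that compartments differ. If significance were compared side by side, the two tests would disagree in roughly 10% to 32% of studies despite equal true effects, against about 5% for a direct contrast. This assumes 80% to 92% power in each compartment and correlation 0 to 0.6. None of these inputs comes from the article, so the range shows why a contrast is needed and does not measure an error in the plan.

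**What to change.** Keep the stratified models. Add one supportive joint mixed model for CCR5:

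- Specimen as a within-woman factor, CVL versus blood. CVL is the specimen used for the power calculation.
- Specimen × time and specimen × method × time terms, with the lower-order terms they imply.
- Specimen-specific variances, and a covariance between the two specimens of one woman.

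Within each method, report the CVL-versus-blood difference in change from visits 1 and 2 to 3, 6 and 12 months, with a 95% CI. Use the same prespecified scale (link) as the primary model. Base any statement that compartments differ on that contrast alone.

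If the joint model is not wanted, state that the compartment comparison is descriptive only and that no claim of a difference will be drawn from separate models.

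The cost is a few sentences and one extra model, with no new samples and no change to the primary test. The drawback is a larger covariance structure, which may be harder to fit with the missing visits the Discussion reports.

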### Power/sample size

For Aim 1, our pilot longitudinal study among women treated with DMPA, LNG-IUD, and ENG-implant provided estimates utilized in sample size calculation. The pilot study evaluated CVL CCR5 levels at four different time points (two visits pre-contraceptive, two visits post-contraceptive) with *n* = 148 total visits [76]. At the pre-contraceptive time point, 23.0% (SD 16.1) of CVL CD4^+^ T-cells expressed CCR5. Post-contraceptive, mean percent of CD4^+^ T-cells expressing CCR5 was 38.3, 34.1 and 23.6 for DMPA, ENG-implant and LNG-IUD, respectively, which represents a 66%, 48% and 3% increase above the pre-contraceptive measurement, respectively [77]. Given 75 women in each contraceptive method arm (DMPA, LNG-IUD, ENG-implant) and allowing for 20% attrition produces a final sample size of 60 women per arm. Assuming the smallest clinically- meaningful change in the percentage of CD4^+^ T cells expressing CCR5 level is 50% and that change will only be observed for DMPA and ENG-implant (not LNG-IUD), produces an effect size of 0.3 (effect SD 2.7). This design achieves 92% power to test the HC method (DMPA, ENG-implant, LNG-IUD) by time (pre-/post-contraceptive) interaction using a Geisser-Greenhouse Corrected F test when significance level is 0.05. Secondary outcomes will be evaluated for direction and magnitude of the associations.

For Aim 2, using the same pilot data, 44% of visits (*n* = 76) had BV present [76]. BV status was consistent with the pre and in post time points (92% concordance) [76]. Mean percent of CD4^+^ T cells expressing CCR5 was 20.3 and 25.1, for no BV and BV present, respectively, with a standard deviation of 15.9 pre-HC and 29.8 and 37.0 with no BV and with BV, respectively, with a standard deviation of 22.1 post-HC [76]. With 75 women in each contraceptive method arm (DMPA, LNG-IUD, ENG-implant), and allowing for 20% attrition, we will have a final sample size of 60 women per arm. Assuming a 0.502 correlation between pre- and post-contraception measurements, 50% of time periods will have BV present, the smallest clinically-meaningful change in proportion of CD4 + T cells expressing CCR5 regardless of BV status is 50% and that a larger change will be observed for BV visits compared to non-BV visits (assuming 85% change vs. 15% change, respectively), producing an effect size of 0.46. This design achieves 87% power to detect a significant BV interaction for the association between each HC method used and CCR5 expression on CD4^+^ T cells using a Geisser-Greenhouse Corrected F test when significance level is 0.05.

## Discussion

The CHIME study design constitutes one of the most comprehensive prospective studies in the field, characterizing immune changes among 225 HIV-uninfected women longitudinally with complementary FGT sampling approaches [15, 77, 78]. Although a randomized controlled study design ensures balance between arms and is therefore commonly adopted in studies of this nature, for feasibility in the US, where a broad contraceptive mix is available and because contraceptive choice is a personal decision, the specific contraceptive type in this study will be left to the preference of participants. However, limitations from non-randomization are minimized by: [1] collecting and controlling for covariates that may impact immune response, including demographics, body mass index (BMI), current STIs, underlying health conditions, vaginal practices (e.g., douching), medication exposure, and semen exposure that could influence outcomes of interest; [2] evaluating two timepoints for each participant prior to contraceptive initiation intended to correspond to follicular and luteal phases, as the optimal non-contraceptive control for comparison; and [3] propensity score methods to adjust for pre-contraceptive characteristics that may be unevenly distributed by contraceptive arm such as STIs as well as behavioral and demographic characteristics.

By design, the study does not directly address the risk of HIV acquisition from hormonal contraceptives; rather, it explores surrogates that might provide a mechanistic explanation for this purported impact of HC use. Being exploratory in nature, the sample size is small, and we may not be able to detect small differences in some of the outcomes. We have carefully selected our markers to focus on our study aims; however, we acknowledge that additional markers may be of interest and can be explored in future evaluations. Furthermore, we acknowledge that many other factors that influence HIV susceptibility warrant further investigation, such as epithelial integrity and endogenous microbicides. We plan to use these banked samples to explore other potential mechanisms in future research. The data generated from the successful completion of this study will be instrumental in the design of a future prospective contraceptive trial to explore HIV acquisition risk and establish safe family planning options for high-risk women.

The COVID-19 pandemic presented unforeseeable challenges for clinical research. Beginning in March 2020, there was a temporary suspension of all research followed by a phased re-initiation of approved studies under stringent social distancing guidelines. During this time, healthcare providers and researchers were required to shift priorities to address and adapt to the immediate needs of the pandemic, including supplementing the existing workforce and staffing COVID wards. These and other personal pressures, such as childcare responsibilities, resulted in staff turnover that coincided with an administrative hiring freeze. While onboarding new staff, the study team focused on maintaining study visits for enrolled participants and processing samples. At the same time, many of our enrolled participants relocated due to job loss, school closures or other COVID-related factors. Those that did not relocate expressed hesitancy regarding attending in-person study visits. Collectively, the pressures of the pandemic on participants resulted in early study terminations or missing visits during the pandemic, requiring the investigative team to re-examine the planned statistical approach and adopt methods that were more robust to missing data. Despite these challenges and limitations, the rich phenotypic and immunologic data collected as part of the CHIME study is poised to help us understand the role of endogenous and exogenous ovarian hormones in regulating immunologic function in the female genital tract.

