## Methods

### Study design and recruitment

The CHIME study, as depicted in Fig. 1, is a prospective cohort evaluating the impact of progestin-based HC methods on immunologic changes in the FGT and systemic compartment. The study aims to recruit 225 HIV-negative women desiring HC, including 75 women in each contraceptive arm (DMPA, ENG-implant, LNG-IUD). The study has been reviewed and approved by the Emory University Institutional Review Board (IRB) and the Grady Health System Research Oversight Committee.

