
In addition to the pelvic evaluation, peripheral venous blood is collected at each visit in two 8 mL cell preparation tubes (CPT; BD Vacutainer™, Becton, Dickinson, and Company) for immunologic markers and hormonal assessment. At visit 1, additional blood is collected in a serum separator tube (SST; BD Vacutainer™, Becton, Dickinson, and Company) for herpes simplex virus (HSV) antibody serology, syphilis testing via rapid plasma reagin (RPR), and HIV antibody/antigen testing (if indicated when the Ora-Quick® is positive or indeterminant).

Collected specimens are immediately stored on ice and are processed for cellular isolation and characterization within four hours. Table 2 lists the schedule of events and biologic specimen collections for the study.

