### Cervical cytobrush processing

Cytobrush samples are processed according to study procedures, then stained with trypan blue stain to check viability and cell count in the automatic cell counter (Invitrogen). The complete sample is used for real time flow cytometry staining.

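### Fresh-cell flow cytometry spans the March 2020 research suspension, but the models name no calendar term, so any shift at the break enters the within-method changes and the time effect

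*Protocol article*

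**What the plan says.** **Duration.** The Abstract states: "Data collection started in March 2019 and is scheduled to be completed in October 2024".

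**When cells are read.** Under Clinical evaluation and specimen collection, specimens go on ice and are "processed for cellular isolation and characterization within four hours". For the cytobrush, "The complete sample is used for real time flow cytometry staining". Biopsy cells are also stained in real time.

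**The break.** The Discussion says that from March 2020 "there was a temporary suspension of all research followed by a phased re-initiation of approved studies", and that staffing and personal pressures "resulted in staff turnover that coincided with an administrative hiring freeze". New staff were brought in while visits and sample processing continued. Participants moved away, were reluctant to attend, left early or missed visits. The one analytic response described is a move to methods that cope better with missing data.

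**The model.** Data analysis says: "Separate models for each outcome will contain time (categorical: visit 1, 2, 3, 4, 5, 6, 7, 8"), with method and the method-by-time interaction. It adds: "Models will additionally include important covariates such as age, race, STI presence, menstrual cycle characteristics". The planned contrasts compare visits 1 and 2 with 3, 6 and 12 months within each method. Method, time and their interaction are each tested at 0.05. Aim 2 uses method-stratified versions of these models and again tests the time main effect at 0.05.

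**The comparator.** The non-contraceptive control is each woman's own two pre-initiation visits.

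**The concern.** Every woman's post-contraception samples are taken later in calendar time than her pre-contraception samples. With no untreated group followed in parallel, the pre/post change within a method is the contraceptive effect plus whatever changed between the two dates: staining, sampling technique, staff or participants' behaviour. Visit number cannot separate the two.

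The dates make this concrete. Collection began in March 2019 and research stopped in March 2020. A woman who started contraception before the suspension therefore has her 12-month visits due at or after it. In the 12-month contrast, the whole pre-suspension cohort straddles the break.

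At stake are the within-method changes at 3, 6 and 12 months and the time main effect in both aims. The method-by-time interaction, which carries the power calculation, is in a different position, because a shift common to all three methods cancels there.

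**Working it through.** **Yardstick.** Power/sample size gives a pre-contraceptive mean of 23.0% (SD 16.1) and a smallest meaningful change of 50%, so the target change is 0.5 × 23.0 = 11.5 points. Changes of 11.5, 11.5 and 0 have mean 7.67. Halved deviations are 1.92, 1.92 and −3.83, with root mean square √[(1.92² + 1.92² + 3.83²)/3] = 2.71, matching the stated effect SD of 2.7. With 180 women and 2 and 177 degrees of freedom, power is 92.6% at an effect size of 0.28 and 95.6% at 0.30, so the stated 92% fits an effect size rounded to 0.3. The power figure is not in dispute.

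**Span.** March 2019 to October 2024 is about 5.6 years. Allowing 12 months of follow-up, enrolment could run about 55 months.

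**Within-method bias (all drift sizes are assumptions).**
- Steady drift: bias = drift per year × years since the pre visits. At 12 months, 2 points a year gives about 2 points and 4 points a year about 4.
- Step at the break: bias = step × share of women with pre visits before it and 12-month visits after it. With uniform enrolment the share is 12/55 = 0.22, so a 10-point step gives 2.2 points.
- The documents do not give the length of the suspension. If samples due in an assumed five-month gap are lost, women with both visits who straddle number 12 − 5 = 7 months' worth out of 55 − 2 × 5 = 45. The share is 7/45 = 0.16, and the bias is 1.6 points.
- No drift: no bias.

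Simulation with 60 women per arm, SD 16.1, correlation 0.5 (Aim 2 states 0.502), uniform enrolment over 4.5 years and no true effect:

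| Assumed shift | Bias at 12 months, within method | False positives, within method | False positives, interaction |
|---|---|---|---|
| none | 0.0 | 4% | 5% |
| 2 points/year | 2.1 | 30% | 5% |
| 4 points/year | 4.2 | 79% | 5% |
| 10-point step | 2.3 | 33% | 5% |

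**Interaction.** Steady drift adds the same amount to every woman's change, so it cancels between methods even if they enrol at different times (simulated: 5% false positives). A step leaves step × difference between methods in the straddling share. In an illustration with DMPA enrolled mainly early, LNG-IUD mainly late, and the step two years in, the shares are:
- DMPA: (1 − 1/4.5)³ − (1 − 2/4.5)³ = 0.30
- LNG-IUD: (2/4.5)³ − (1/4.5)³ = 0.08

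The bias is 10 × 0.22 = 2.2 points (simulated 2.3, with about 13% interaction false positives). The actual suspension came one year in. Under the same extreme pattern the shares are 1 − (1 − 1/4.5)³ = 0.53 and (1/4.5)³ = 0.01, so the bias would be about 5.2 points. The documents do not say that enrolment timing differed by method.

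**Effect of adjustment.**
- Before/after indicator, assumed 10-point step: bias falls from 1.6 to about 0.1 points and false positives from 20% to about 7%. The standard error rises by about 1%, or about 9% if timing differs strongly by method.
- Linear date plus period terms: bias falls to about 0 to 0.2 points. The standard error rises from 1.47 to 1.65 (1.65/1.47 = 1.12), or to 1.73 (1.18) with timing that differs by method.
- Smooth date term: about 9% more standard error, and about 1.5 points of new bias if later enrolees differ by an assumed 5 points.

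**The case against.** The best defence has four parts.

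1. No drift is shown. Staff turnover is not placed in the cytometry laboratory, and the article fixes the antibody clones, cytometer, software version and dead-cell exclusion. This stands: the size is unknown and every figure above is conditional. Laboratory blinding to method, also cited in defence, prevents reading that differs by method but does not prevent a calendar shift.

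2. The covariate list is open, and batch or instrument terms are often left to a fuller document. That is fair for operator and reagent-lot terms, which are not pressed here. It is weaker for the break itself: the article specifies the time variable, contrasts and alpha, reports the disruption, and describes only a missing-data response.

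3. The powered interaction is largely protected. This stands. A reader might infer that the interaction absorbs drift in general, or that free choice of method made the arms fill at different times. The documents support neither.

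4. The problem might be solvable in the laboratory. A reader might infer from fresh staining that no genital sample can be re-assayed. The documents contradict that: CVL processing freezes leftover cells, PBMCs are stored, and gating is done in software after acquisition. Only the cytobrush sample is stated to be used up. Whether enough stored cells remain is not said.

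It is also fair that lost visits during the pandemic reduce the number of straddling women who contribute 12-month data.

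**Conclusion.** The concern holds for the within-method pre/post changes and the time main effect in both aims. Nothing in the stated design or models separates time on contraception from calendar time, and a known break falls one year into collection.

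Under an assumed 10-point step and similar enrolment timing across methods, the 12-month within-method bias is about 1.6 to 2.3 points, or 14% to 20% of the 11.5-point target (1.6/11.5 and 2.3/11.5). With no shift it is zero. The method-by-time interaction is biased only if an uneven shift and method-specific enrolment timing occur together.

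A reader might conclude that the planned results are already distorted. The documents do not support that: they record a disruption, not a change in measured CCR5. This is an unguarded exposure that the analysis can largely close.

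**What to change.** 1. Add to the Aim 1 and Aim 2 CCR5 models an indicator for whether the sample was taken before the March 2020 suspension or after restart. Staggered enrolment puts the same visit number in both periods, so the term can be estimated.
2. Report as a sensitivity analysis the women whose pre and post visits all fall in one period. For the 12-month contrast these will in practice be women enrolled after restart.
3. Use a smooth calendar-date term only as a further sensitivity analysis. Within a woman, date and time on study move together, so this term rests on comparing women enrolled at different dates and can be biased if later enrolees differ.

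**Cost.** The change is to analysis wording and needs only sample dates. It is cheap but not free: standard errors rise by about 1% with the indicator, about 9% if enrolment timing differs strongly by method, and about 9% to 18% with smooth or linear date terms. The indicator assumes one shift common to all methods and will not remove gradual drift. The single-period analysis uses fewer women.
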